# REhabilitation of Dysphagia with ACupuncture and auricular Therapy after severe acquired brain injury (REDACT study): a double-blind randomized controlled trial protocol

**DOI:** 10.3389/fneur.2026.1724043

**Published:** 2026-02-24

**Keywords:** acupuncture, auriculotherapy, dysphagia (swallowing disorder), severe acquired brain injuries, tracheal cannula, rehabilitation

## Abstract

**Clinical trial registration:**

https://clinicaltrials.gov/ct2/show/NCT06888219, NCT06888219.

## Introduction

Neurogenic dysphagia, defined as a swallowing disorder resulting from neurological disease, is a common complication following severe acquired brain injury (sABI) (1, 2). Its prevalence in this population has been estimated at approximately 93% and may reach up to 99% in patients with disorders of consciousness (DoC) (3) at admission to intensive rehabilitation units (IRUs) (4). In patients with sABI, dysphagia increases the risk of malnutrition and dehydration and is associated with higher morbidity, longer hospital stays, and increased healthcare costs (5–8) so enteral tube feeding is commonly employed to mitigate these risks (9, 10). However, although some swallowing disorders are clinically apparent, silent aspiration—defined as aspiration in the absence of a cough reflex—may occur in up to 50% of patients after sABI (11) and can even arise without oral intake, thereby increasing the risk of respiratory infections and mortality (8).

Swallowing disorders are recognized by the World Health Organization as a medical disability with major psychological and social consequences, negatively affecting quality of life (12) and the rehabilitative management of dysphagia represents therefore a central goal during the stay in the IRU. In patients with sABI who remain in a DoC or evolve into a confusional state (13) this goal is often limited by poor cooperation. Conventional rehabilitation approaches (14) require varying levels of patient collaboration, which is frequently compromised in sABI.

It should be noted, however, that patient cooperation is not necessary to achieve oral feeding. Several studies have examined the impact of cognitive level on oral feeding recovery (15). While a cognitive threshold equal to or higher than level 4 on the Rancho Los Amigos Cognitive Functioning Scale (LCF) was initially deemed necessary (2), more recent studies have extended the possibility of oral feeding recovery to patients in a minimally conscious state (16, 17). According to the latest evidence, only patients with unresponsive wakefulness syndrome are very difficult, if not impossible, to rehabilitate with respect to dysphagia (18, 19). Another factor closely related to swallowing that should be taken into consideration during dysphagia rehabilitation in this patient population is the presence of a tracheal tube. Fifty to 70 % of patients with sABI are tracheotomized at the time of transfer to the IRU (4), and its presence has been shown to be closely related to dysphagia in a bidirectional manner (20–22). Tracheotomy can affect the physiology of swallowing, while impaired saliva management and persistent dysphagia remain major obstacles to successful decannulation, even in the long term (23). The inability to swallow saliva can lead to iatrogenic sialorrhea or excessive saliva accumulation (24), resulting in stagnation in the oral cavity that promotes excessive salivation, skin irritation, choking, impaired oxygenation, and even life-threatening pneumonia (25).

Given the clinical complexity and heterogeneity that characterizes this population, the rehabilitation of dysphagia in patients with sABI outcomes represents a considerable challenge (26).

In this context, acupuncture and auricular (AA) therapies emerge as innovative therapeutic options, applicable even in non-collaborative patients, including those in a minimally conscious state and with tracheal tubes, and are grounded in neuroscientific principles aimed at promoting the recovery of swallowing (27). Although a substantial body of evidence supports the potential of acupuncture as a complementary treatment to improve swallowing function, current studies and reviews focus primarily on post-stroke patients (28–32), while evidence in sABI remains limited. Some exploratory studies in patients with traumatic brain injury or DoC have investigated acupuncture-based interventions, reporting indications of possible improvements in arousal or oro-facial responsiveness (33, 34), although findings remain preliminary. In addition, a small number of Chinese clinical studies have examined acupuncture techniques for dysphagia after craniocerebral injury, describing potential benefits in selected patient groups (35, 36). Despite growing interest in AA for dysphagia, no randomized controlled trials have assessed its efficacy in sABI patients with tracheal cannulas and severe dysphagia. This trial aims to evaluate acupuncture plus auriculotherapy in severely dysphagic patients with vascular sABI admitted to an IRU.

## Materials and methods

### Study design, setting and participants

This multicenter, longitudinal, randomized, controlled, patient- and assessor-blinded trial (ClinicalTrials.gov: NCT068882) aims to evaluate whether combining AA with standard logopedic therapy is superior to usual care alone for rehabilitating dysphagia in vascular sABI patients with a tracheal cannula. The protocol was developed in accordance with the SPIRIT 2025 (Standard Protocol Items: Recommendations for Interventional Trials) guidelines (37) and STRICTA (Standards for Reporting Interventions in Clinical Trials of Acupuncture) recommendations (38). Patients admitted to the IRU of the IRCCS Fondazione Don Carlo Gnocchi in Florence will be considered for screening. Eligibility will be determined based on predefined diagnostic, inclusion, and exclusion criteria as outlined below.

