### Statistical analysis

At present, we have designed a pilot study with the purpose of providing preliminary data necessary to calculate the appropriate sample size for a subsequent randomized controlled trial (RCT). The main study will be a 2-arm, randomized, controlled trial for which a medium effect size was conservatively hypothesized. According to the stepped rules of thumb proposed to estimate the size of the pilot based on Cohen’s d effect size (55), for an 80% power main trial, the pilot sample size should be 10 per arm, and the subsequent main trial will require somewhere between 34 and 176 participants per arm. The sample size of 10 participants per arm will be increased to 12 participants per arm to account for potential dropouts. This sample size was determined exclusively since methodological recommendations available in the literature. The data obtained from this pilot study will be used to estimate the effect size and variability, which will inform the power analysis and the determination of the required sample size for the definitive RCT. Analyses will be conducted using SPSS version 28 software (SPSS, SPSS Inc., Chicago, United States). The normality of the distribution of continuous variables will be checked using the Shapiro–Wilk test. If the variables violate the assumption of normality, they will be presented through their median value and interquartile range, otherwise through mean and standard deviation. Categorical variables will be represented through absolute frequencies and percentages. Baseline characteristics will be compared between treatment and control groups using independent *t*-tests or Mann–Whitney U tests for continuous variables, depending on data distribution, and chi-square or Fisher’s exact tests for categorical variables. The primary outcome (improvement in dysphagia) will be assessed by comparing MASA scores and “Pooling score” between groups at T1 using ANCOVA models (adjusting for baseline values) or non-parametric alternatives, if assumptions are not met. Maintenance of the effect at T2 will be evaluated using linear mixed models with random intercepts, including group, time (baseline, T1, T2), and their interaction as fixed effects; if model assumptions are violated, change scores between T1 and T2 will be calculated and compared between groups using independent *t*-tests or Mann–Whitney U tests. Secondary outcomes will be analyzed as follows: decannulation rates at T1 and T2 will be compared between groups using chi-square or Fisher’s exact tests, while decannulation times will be compared using independent *t*-tests or Mann–Whitney U tests and Kaplan–Meier survival analysis. Infection rates at T1 and T2 will be compared between groups using chi-square or Fisher’s exact tests. Functional autonomy at T2, measured by the GOS-E, will be compared between groups using independent *t*-tests if normality assumptions are met, or Mann–Whitney U tests otherwise. A *p*-value <0.05 will be considered significant in all analyses. The primary analysis will follow the intention-to-treat (ITT) principle. Sensitivity analysis will be performed to assess the robustness of the findings, including per-protocol analysis restricted to patients who completed the assigned intervention.

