## Discussion

The rehabilitation of dysphagia in patients surviving a sABI presents a significant challenge, particularly when initiated in the early phase in which patient cooperation is minimal or absent. In such cases, speech-language rehabilitation techniques requiring active patient participation are not feasible. Instead, passive or neuromodulation-based approaches must be considered. Within this context, acupuncture and auriculotherapy emerge as promising treatment options since these therapies do not rely on patient cooperation. The main purpose of this study is to determine whether acupuncture and auriculotherapy can serve as an appropriate and effective treatment for rehabilitating dysphagia in non-communicative patients surviving a sABI.

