## Conclusion

Dysphagia is a significant disability for patients with sABI, and its management is crucial, particularly in the early stages of rehabilitation. Acupuncture and auriculotherapy offer promising avenues to enhance interdisciplinary care for these patients, being cost-effective, easily administered at the bedside, associated with minimal side effects and without adding pharmacological burden. This randomized double-blind trial proposes to explore the clinical effectiveness and feasibility of these techniques as part of an integrated rehabilitation approach.

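### The protocol states a superiority and effectiveness aim judged at p<0.05, but describes and sizes the study as a pilot of 10 to 12 per arm that cannot meet that aim

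*Protocol article*

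**What the plan says.** The protocol article gives the purpose of the study in four places, and they do not agree.

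- Study design, setting and participants: the trial "aims to evaluate whether combining AA with standard logopedic therapy is superior to usual care alone for rehabilitating dysphagia".
- Statistical analysis: "we have designed a pilot study with the purpose of providing preliminary data necessary to calculate the appropriate sample size" for a later randomised trial.
- Discussion: "The main purpose of this study is to determine whether acupuncture and auriculotherapy can serve as an appropriate and effective treatment".
- Conclusion: the trial "proposes to explore the clinical effectiveness and feasibility of these techniques".

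In the text at hand the word pilot occurs only in Statistical analysis. The title calls the study a double-blind randomised controlled trial.

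The sample size follows the pilot description. The medium effect belongs to the main trial, "for which a medium effect size was conservatively hypothesized", and the rule applied is that "for an 80% power main trial, the pilot sample size should be 10 per arm", raised to 12 for dropout. The section adds that "the subsequent main trial will require somewhere between 34 and 176 participants per arm".

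The analysis follows the efficacy description. MASA and the Pooling score are compared between arms at T1 by ANCOVA adjusted for baseline, with non-parametric alternatives. The secondary outcomes are tested between arms as well. Of the p-value the section says: "value <0.05 will be considered significant in all analyses". It does not call any test exploratory.

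**The concern.** A superiority aim, a between-arm test and a significance threshold together make a decision rule, and a reader will judge the result by it. With 10 to 12 patients per arm that rule says little in either direction.

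A non-significant result would be likely even if acupuncture plus auricular therapy (AA) had a moderate benefit, yet it would be read against a stated superiority aim. A significant result could arise only from a large observed difference, so it would tend to overstate the benefit. The plan also uses the estimated effect size for the power calculation of the definitive trial, so an overestimate could make that trial too small.

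**Working it through.** **Inputs from Statistical analysis:** 10 per arm, 12 with dropout; threshold 0.05; main trial at 80% power with 34 to 176 per arm; primary analysis by ANCOVA on baseline. The 1:1 ratio comes from the randomisation section.

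**Not stated, so assumed:** a two-sided test; d = 0.5 for medium, with a range of 0.3 to 0.7 (step 1); a baseline-to-T1 correlation r of 0.3 to 0.7.

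**Step 1. Reproduce the plan's own figure.** The normal approximation is n per arm = 2(1.960 + 0.842)²/d² ≈ 15.7/d².

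- d = 0.3: 15.7/0.09 ≈ 174.4, rounded up to 175; exact t-test 176.
- d = 0.7: 15.7/0.49 ≈ 32.0, just above 32 and so rounded up to 33; exact t-test 34.

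Both stated ends reproduce exactly with the two-sided t-test. One-sided tests would give 139 and 26, so the plan's figures are two-sided and its range corresponds to d of about 0.3 to 0.7. At d = 0.5 the same method needs 64 per arm.

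**Step 2. Power of the present study, unadjusted.** The test statistic is noncentral t with 2n − 2 degrees of freedom and noncentrality d√(n/2). At d = 0.5:

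- n = 10: noncentrality 0.5 × √5 = 1.118, critical t (18 df) 2.101, power 18.5%.
- n = 12: noncentrality 0.5 × √6 = 1.225, critical t (22 df) 2.074, power 21.6%.

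**Step 3. Power with the planned ANCOVA.** Replace d by d/√(1 − r²) and take one degree of freedom less. For d = 0.5 this gives 0.524, 0.577 and 0.700 at r = 0.3, 0.5 and 0.7.

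Power at 10 / 12 per arm:

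| True d | Unadjusted | ANCOVA, r = 0.3 | ANCOVA, r = 0.5 | ANCOVA, r = 0.7 |
|---|---|---|---|---|
| 0.3 | 9.7% / 10.8% | 10.2% / 11.4% | 11.3% / 12.8% | 14.4% / 16.6% |
| 0.5 | 18.5% / 21.6% | 19.8% / 23.2% | 23.0% / 27.1% | 31.5% / 37.3% |
| 0.7 | 31.7% / 37.5% | 34.1% / 40.3% | 40.0% / 47.2% | 54.3% / 62.9% |

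No cell reaches 80%. Unadjusted, 80% power needs d = 1.32 at 10 per arm or 1.20 at 12 per arm.

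**Step 4. Precision.** The half-width of the unadjusted 95% confidence interval, in SD units, is t × √(2/n): 2.101 × √0.2 = 0.94 at 10 per arm and 2.074 × √(1/6) = 0.85 at 12. These are also the smallest observed differences that could be significant, that is 0.94/0.5 = 1.9 and 0.85/0.5 = 1.7 times a true effect of 0.5. The chance of a non-significant result at d = 0.5 is 100 − 18.5 = 81.5% or 100 − 21.6 = 78.4%, about four in five.

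**The case against.** The best defence is that Statistical analysis is open about the study: it says pilot, says the size rests on published recommendations, and says that a definitive trial must follow. The Conclusion speaks only of exploring. Estimating an effect size is a declared use of the data, so comparing the arms is not in itself inconsistent with a pilot. All of this stands, and it limits the point. It does not reconcile the superiority aim in the design section or the main purpose in the Discussion, and it leaves an unqualified significance rule in place.

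A reader might infer more than the article supports:

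- *That the study misses its own power target.* It has none. The medium effect is hypothesised for the main trial and no d is given, so every power figure above is conditional.
- *That 19–22% is the power of the planned analysis.* Those figures are for an unadjusted comparison. ANCOVA is planned and does better, though not enough.
- *That sizing a later trial is the only purpose of the pilot.* The section does not say so. Its word for exclusivity describes how the sample size was chosen.
- *That 10 per arm is an arithmetic error.* It is a rule of thumb, and the main-trial range quoted with it reproduces.
- *That a null result will be reported as lack of superiority.* No section says this. It is a risk created by the wording.
- *That feasibility endpoints or progression criteria have been omitted.* An article may leave these to the full protocol. Attendance and adverse events are already recorded.

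**Conclusion.** The inconsistency is real and is in the article's own words: it states a superiority and effectiveness aim with a p<0.05 rule for a study that it elsewhere calls a pilot and sizes at 10 to 12 per arm, against 34 to 176 for the main trial.

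At an assumed d = 0.5, two-sided power is about 19–22% unadjusted and about 20–37% under ANCOVA with r from 0.3 to 0.7. Over d from 0.3 to 0.7, unadjusted power is about 10–37%. The conclusion does not depend on the exact d or r: even the most favourable cell of the table, d = 0.7 with r = 0.7, gives 54–63%. The design can therefore estimate an effect imprecisely but cannot decide superiority. What needs correcting is the aim and the decision rule, not the sample size.

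**What to change.** 1. In Study design, setting and participants, in the Discussion and in the Conclusion, restate the aim as that of a pilot randomised trial that estimates the between-group effect and its variability for the main trial.
2. In Statistical analysis, make point estimates with 95% confidence intervals the primary report, label all p-values exploratory, and state that no conclusion on superiority or effectiveness, positive or negative, will be drawn from this study.
3. For the feasibility aim in the Conclusion, report descriptively what the planned data already provide: session attendance, adverse events, and completeness of MASA and FEES at T1 and T2. Formal progression criteria are optional.

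The change needs no extra patients, visits or measurements, only consistent wording wherever the aim is repeated. The cost is giving up an efficacy claim that the design cannot support. If the sponsor wishes to keep the superiority aim, the trial has to be sized for it, which at d = 0.5 unadjusted means 64 per arm before dropout.

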#### Diagnostic criteria

sABI (39) of vascular etiology (ischemic or hemorrhagic), ascertained by Computerized Tomography or Magnetic Resonance examination.Severe dysphagia, documented by a Food Oral Intake Scale (FOIS) score = 1.DoC or non-collaborative state, defined by LCF ≤ 4.

#### Inclusion criteria

Time between acute event and enrolment <3 months.Age >18 years.Presence of tracheal cannula at study enrollment.Signature of informed consent by legal representative.

#### Exclusion criteria

Instability of general clinical conditions (mechanical ventilation, sedation, sepsis, sub-emergent epileptic seizures).UWS, according to the Coma Recovery Scale – Revised (CRS-R) (40).Known fear of needles (agophobia), as reported by the patient’s legal representative.

Patient’s legal representatives will receive written and oral information about the study aims, interventions, potential risks, and rights. Informed consent will be obtained before enrollment. All subjects will undergo an initial evaluation (T0), an evaluation at 4 weeks (T1) and a follow-up at 3 months (T2) (see Figure 1).

**Figure 1 fig1:**
[figure not shown]
Study timeline. sABI, severe acquired brain injury; LCF, level of cognitive functioning; FOIS, food oral intake scale; UWS, unresponsive wakefulness syndrome; CRS-R, coma recovery scale – revised; DRS, disability rating scale; FIM, functional independence measures; MASA, Mann assessment ofswallowing ability; EEG, electroencephalography; MEP, motor evoked potentials; EMG, electromyography; FEES, fiberoptic endoscopic evaluation of swallowing; GOS-E, Glasgow outcome scale-extended.

### Clinical and instrumental assessments

Assessments will be performed at recruitment (T0), after the 4 weeks (T1) and after 12 weeks (T2).

Clinical evaluation (planned at T0, T1 and T2) will be supported by the clinical scales recommended by the Italian Society of Physical and Rehabilitation Medicine (41) and includes the CRS-R and the LCF, the Disability Rating Scale (DRS) and the Functional Independence Measures (FIM). Dysphagia will be assessed by the Mann Assessment of Swallowing Ability (MASA) Scale and the FOIS. At T2, the Glasgow Outcome Scale-Extended (GOSE-E) (42) will be performed.

The instrumental evaluations will include the Fiberoptic Endoscopic Evaluation of Swallowing (FEES) (43) integrating the compilation of the Pooling score.

To identify possible confounding factors such as Epileptic status and Intensive Care Unit-Acquired Weakness may interfere with the swallowing function, other data will be recorded from instrumental exams included in the routinary clinical practice (standard electroencephalography-EEG and Electroneuro/myography-ENG/EMG) (44).

Finally, the decannulation achievement and its timing and the infection rate will be recorded.

For the purposes of this study, infections will be recorded as clinical events requiring initiation or escalation of systemic antibiotic therapy supported by clinical signs and, when available, microbiological sampling. Pneumonia will be recorded when respiratory infection is the primary suspected source and is supported by: (i) new or progressive and persistent pulmonary infiltrate/consolidation on chest imaging; (ii) at least two of the following: fever or hypothermia, leukocytosis/leukopenia, purulent respiratory secretions or increased suctioning needs, worsening gas exchange/increased oxygen requirement, or new/worsening cough/dyspnea/tachypnea; with (iii) microbiological support when available (e.g., positive culture from respiratory secretions).

All evaluations will be performed by professionals blinded to the treatment/control arm. Moreover, patients enrolled in the study, given their state of unconsciousness and behavioral/cognitive confusion, may be considered blinded for the purpose of the received AA treatment.

### Randomization, allocation concealment and blinding

After enrollment, patients will be allocated to one of two groups by computerized randomization and stratified by MASA scale, with an allocation ratio of 1:1, and assigned to either the control or intervention arm. Allocation concealment will be ensured via sequentially numbered, opaque, sealed envelopes prepared by an independent statistician (see Figure 2). The study is designed as double-blind: all clinical and instrumental assessments will be performed by professionals blinded to the treatment arm, and patients are considered blinded either because they present a DoC or due to severe cognitive impairment with short-term memory deficits, which prevent them from being aware of or recalling the treatment received. Due to the nature of the acupuncture intervention, blinding of the acupuncturist is not feasible and represents a potential source of performance bias. To minimize its impact, several mitigation strategies were implemented *a priori*. Acupuncturists will not be involved in outcome assessment, rehabilitation planning, or data analysis. The intervention will be delivered according to a standardized protocol, including fixed session duration, predefined acupuncture points, and uniform treatment setting. Outcome assessors and the rehabilitation team will remain blinded to group allocation throughout the study. Any accidental unblinding will be documented.

